#### **Sensitivity Analysis**

Sensitivity analyses will be carried out for the analyses of the primary trial objectives. We will test whether any intervention superiority or non-inferiority with regards to PTSD and MDD diagnoses is robust/ holds when 1) analysing data including cases with missing data, 2)

[name], [name], [name], [name], [name], [name], [name], [name], [name], [name], [name], & [name] Cognitive resilience training to prevent PTSD and MDD in paramedics: A randomised controlled trial.

analysing data including any potential covariates that are predictive of any missing data, and  
3) imputation.

### **Pre-specified Subgroup Analysis**

Intervention effects of iCT-R on PTSD and MDD diagnoses at 1-year follow-up (short-term primary outcome time point) and at 2-year follow-up (once completed, long-term primary outcome time point) are presented using forest plots for participants who had higher versus lower PTSD or MDD symptom severity at baseline.

### **Supplementary/ Additional Analyses and Outcomes**

Additional exploratory analyses due to the Covid pandemic, suggestions taken from [FDA](#) guidelines (June 2020) [22] and Mayer et al. (2020) [23] and adapted to the needs of the current trial:

The trial took place before and during the outbreak of the Covid pandemic. Additional reporting of descriptive statistics and missing data, additional exploratory analyses, and sensitivity analyses are needed to capture any possible impact of the pandemic on the main trial objectives.

Two Covid periods (pre-Covid/ before March 2020, which marks the first UK national lockdown, or possibly after-Covid, coded as ‘0’, and during-Covid, since March 16, 2020, coded as ‘1’) are defined. For each participant at each assessment time point it will be classified whether the assessment took place before or after Covid impact versus during Covid impact. This way exogeneous time-varying covariates are generated for further analyses.

Additionally, a COVID questionnaire was implemented to capture any possible subjective impact by COVID reported by the participants on outcome.

## Main trial analyses and Covid:

Descriptive statistics for the two outcome measures for the primary trial objectives (PTSD and MDD diagnoses and PTSD or MDD symptom severity) are reported for the whole sample and by intervention groups based on the Covid grouping variables for the short-term primary outcome time point at 1-year follow-up and the 2-year follow-up assessment point, once completed (means and standard deviations for continuous outcomes and absolute numbers and percentages for diagnoses).

In the case of any differences, additional analyses are carried out to explore whether there is any possible intervention heterogeneity depending on participants' Covid status on PTSD and MDD diagnoses or PTSD and MDD symptom severity at 1-year follow-up or at 2-year follow-up, once completed. In this case, linear and logistic mixed models are specified in the same way as proposed for the analyses of the primary trial objectives and participants' Covid status variables are entered as exogenous time-varying covariates. Two-way interaction terms between those covariates and intervention group as well as three-way interaction terms between Covid status, time, and intervention group are analysed. In the case of significant interaction terms, which could possibly indicate intervention heterogeneity, additional effect size measures are reported. Adjusted mean differences and Cohen's  $d$ 's with standard deviation at baseline in the denominator are reported in tables for continuous outcomes from results of linear mixed effects models and frequencies of diagnoses (absolute numbers and percentages) and absolute differences as well as odds ratios are reported for dichotomous outcomes.

In addition to Covid status depending on time points, the COVID questionnaire, scored as a continuous variable, which assesses the self-reported impact of COVID on a participant will be descriptively reported and analysed as a covariate in a similar way like the time-based covariates to determine whether or not it influences outcome. We will compare rates of PTSD and MDD for the sample who score positive on the item ('I am graduating

early as a result to support the NHS workforce') compared to participants who do not endorse this item.

Exploration of missing data patterns and possibly additional sensitivity analyses:

Additional missing data explorations are reported. Any missing data, withdrawal from the intervention, or loss to follow-up are reported in tables for the whole sample and by intervention groups based on the Covid status variables for the short-term primary outcome time point 1-year follow-up and the 2-year follow-up assessment point, once completed (means and standard deviations for continuous outcomes, absolute numbers and percentages for dichotomous outcomes).

In the case of any missing data, withdrawal, or loss to follow-up dependent on Covid status or the endorsement of the COVID questions, additional sensitivity analyses need to be carried out.

CACE analyses:

In the case of potential intervention heterogeneity due to any influence of the Covid pandemic, additional CACE analyses are carried out, as well, to test whether Covid status or questions had an influence on compliance to the interventions. In case of any differences the Covid CACE is compared with the intent-to-treat intervention effects resulting from the primary trial analyses and results are reported.

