| Planned Trial Period               | 16 October 2017 – 30 th January 2021                                                                                                                                                                                                                                                                                                                                                                                                 |                                                                                                                                                                                                              |
|                                    | Objectives                                                                                                                                                                                                                                                                                                                                                                                                                                      | Outcome Measures                                                                                                                                                                                             |
| Primary                            | 1. Is internet-delivered cognitive training for resilience (iCT-R) more effective than accessing already available mental health information (Mind-Online) or having no specific training (standard practice), i.e., does iCT-R lead to fewer cases of PTSD and Major Depression (including subsyndromal PTSD and MD) and less PTSD and MD symptomatology at follow-up compared to Mind-Online and standard practice control conditions? | 1. Primary: Structured Clinical Interview for DSM-5 – PTSD and MD modules 

PTSD Symptom Checklist (PCL-5) 

Patient Health Questionnaire (PHQ-9)  |

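### Arm effects adjusted for the self-reported COVID impact score should not be read as treatment effects

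*Combined protocol and SAP*

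**What the plan says.** SAP section 6.6 (Supplementary/Additional Analyses and Outcomes) sets up two Covid variables.

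- **Date-based status.** Each assessment is classed by its date, with the Covid period coded as "during-Covid, since March 16, 2020". The SAP adds: "This way exogeneous time-varying covariates are generated for further analyses".
- **Questionnaire.** Separately, "a COVID questionnaire was implemented to capture any possible subjective impact by COVID reported by the participants on outcome".

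Under the subheading on the main trial analyses and Covid, if descriptive differences appear, mixed models built like the primary ones are fitted. In these, participants' "Covid status variables are entered as exogenous time-varying covariates", and the following are analysed: "Two-way interaction terms between those covariates and intervention group as well as three-way interaction terms between Covid status, time, and intervention group". Effect sizes are reported if an interaction is significant.

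The questionnaire, scored as a continuous variable and "which assesses the self-reported impact of COVID on a participant", then "will be descriptively reported and analysed as a covariate in a similar way like the time-based covariates". The stated aim is to find out whether it affects outcome. The SAP adds no caution for the score and names no mediation or other causal method for it. The whole Covid section is labelled exploratory, and the covariates listed for the primary models in sections 3.7 and 6.2 do not include the score.

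**The concern.** The calendar fixes the date-based status, so no arm can alter it. The score is a participant's own rating of how the pandemic affected them. SAP section 3.1 says iCT-R is meant to modify rumination and appraisals, and section 3.2 accepts that participants cannot be fully blinded. On the trial's own hypothesis the training could change such a rating. Current distress could change it too, which would make the score partly a reflection of the outcome.

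If the score is handled like the date-based status, the arm coefficient is conditioned on something that randomisation does not balance. That coefficient estimates a different quantity from the intention-to-treat effect. A reader checking whether the result held up during the pandemic could take a weakened adjusted contrast as evidence that it did not, or a score-by-arm interaction as evidence that the pandemic changed the effect.

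**Working it through.** **1. The plan's own figures.** The point disputes none of them, but 152 per arm is used below. Protocol section 11.2 gives 25% in controls and a 50% relative reduction, so 12.5% with training.

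- Odds ratio: (0.125/0.875)/(0.25/0.75) = 0.429, as stated.
- Two-sided 5%, 80% power, no continuity correction, mean proportion 0.1875: n = [1.96 x sqrt(2 x 0.1875 x 0.8125) + 0.842 x sqrt(0.25 x 0.75 + 0.125 x 0.875)]^2 / 0.125^2 = 151.9, so 152 per arm and 304 for two arms.
- 3 x 152 = 456, and 456/0.80 = 570. All reproduce.

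**2. When the score was collected.** The documents give no administration date. The planned trial period starts on "16 October 2017" (protocol synopsis) and the Covid period on 16 March 2020. The SAP version label reads 21 April 2021, and section 3.5 already gives 1-year diagnosis rates for the total sample. Participants contributing those rates were therefore randomised by about April 2020. Assuming the questionnaire was not in use before the Covid period, it could precede randomisation only for anyone randomised in roughly the last five weeks of that window. Collection after randomisation is thus a strong inference, but still an inference.

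**3. Size by path algebra.** All three inputs are assumptions, since the documents give none: true effect on symptoms -0.30 SD, training shifts the score by a, and slope b of symptoms on score. Adjusted effect = -0.30 - a x b.

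| a (SD) | b | Adjusted effect | Removed |
|---|---|---|---|
| 0 | 0.3 or 0.5 | -0.30 | 0% |
| -0.2 | 0.3 | -0.24 | 20% |
| -0.2 | 0.5 | -0.20 | 33% |
| -0.3 | 0.3 | -0.21 | 30% |
| -0.3 | 0.5 | -0.15 | 50% |
| -0.4 | 0.3 | -0.18 | 40% |
| -0.4 | 0.5 | -0.10 | 67% |

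**4. Size by simulation, also under assumed inputs.** Here the score has no effect of its own. A latent distress variable loads on both score and outcome (0.5 on each, or 0.7 on each), and training lowers the score by 0.2 or 0.4 SD. The slope within arm is the product of the loadings, 0.25 or 0.49, so the expected bias runs from 0.2 x 0.25 = 0.05 to 0.4 x 0.49 = 0.196.

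- Simulated with 400,000 participants, a true -0.30 becomes -0.25 to -0.10 and a true null becomes +0.05 to +0.20. With no shift and the same distress-score link in both arms, there is no bias.
- With 152 per arm, a 0.4 SD shift and 4,000 runs, the adjusted arm test rejects a true null in 15% (loading 0.5) or 49% (loading 0.7) of runs. Power for -0.30 SD falls from about 74% to 42% or 18%.
- For a binary outcome with true odds ratio 0.429, the adjusted odds ratio is 0.46 to 0.57. Part of any such change is not bias: with no shift and an unchanged link it was already 0.43 or 0.37, because an odds ratio changes when any prognostic variable is added.

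**5. Score-by-arm interaction, with no true heterogeneity.**

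- If training only shifts the score, the linear-model test rejects in about 5% of runs.
- If training also halves the loading of distress on the score (0.7 to 0.35), the slope in the trained arm is (0.35 x 0.7)/(0.35^2 + 0.51) = 0.245/0.6325 = 0.387, against 0.490 in controls. The interaction coefficient is then about -0.10, and the test rejects in about 14% of runs.
- Rejection rates for the logistic interaction were not computed.

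**The case against.** The strongest reply is that the SAP claims little for this analysis. It applies the word exogenous only to the date-based status, and the three-way interaction is written for that status. The score is brought in as an addition, with the aim of seeing whether it relates to outcome. A score-by-arm term is the likely reading of handling it in a similar way, but it is never spelled out. Nowhere does the SAP say that the treatment effect will be taken from a score-adjusted model. The robustness question is approached first through descriptive tables and then the date-based models, so it does not rest on the questionnaire. The one item quoted, on graduating early, records an event more than an appraisal, and the item list and scoring are not given. The assumed 0.4 SD shift would also have training move the COVID rating more than the symptoms it targets (0.30 SD).

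All of this stands as a limit on scope and size. What remains is that the only rule given for the score points to models in which the arm effect is conditioned on it, with nothing to say how that arm effect should be read.

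**Conclusion.** The point holds as a modest one, confined to the exploratory Covid analyses. An arm effect adjusted for the COVID impact score is not the intention-to-treat effect and may be biased. This rests on two inferences: that the score was collected after randomisation, and that training or current distress can affect it. The size cannot be fixed from the documents. The assumed inputs give a loss of 0% to 67% of a -0.30 SD effect, and zero is a legitimate value.

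A reader might infer three stronger things that the documents do not support.

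- **That the SAP declares the score exogenous.** It does so only for the date-based status; the score is linked to it by similarity of handling.
- **That the heterogeneity tests are biased in general.** Those using the date-based status are not in question. For the score, a linear-model test keeps its size under a pure shift and is distorted only if training also changes how the score relates to distress. In either case the interaction is not clean evidence that the pandemic modified the effect.
- **That the trial's main result is at risk.** The primary intention-to-treat models omit the score, and the sample size of 570 is unaffected.

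**What to change.** Amend the wording of SAP section 6.6:

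- Use only the date-based Covid status for adjustment and effect modification in the Covid treatment-effect models.
- Report the questionnaire score descriptively by arm, as a post-randomisation outcome. Descriptive reporting is already planned; the split by arm is the addition.
- Do not present score-adjusted arm contrasts as treatment effects, or score-by-arm interactions as effect heterogeneity.
- Label any further use of the score as association or mediation, with its assumptions stated. Stating when the questionnaire was given would settle the timing question.

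The cost is a wording change. One exploratory adjusted contrast is given up as an estimate of the treatment effect. No new data are needed.

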#### 7.1.1 Inclusion Criteria

- Aged 18 and above.
- In years 1, 2 or 3 of student paramedic training.
- Access to internet.
- Willing to be randomly allocated.

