## **Randomisation and Blinding**

Participants are randomised on a 1:1:1 ratio as per a computer-generated randomisation schedule by OCTRU (Oxford Clinical Trials Research Unit) stratified by site, gender and baseline PHQ-9 score ( $\geq 9$  vs.  $< 9$ ) and PCL-5 score ( $\geq 33$  vs.  $< 33$ ). The researchers inform participants of the intervention they are to receive after participants have completed baseline assessments. Outcome assessment is single blind. Online questionnaires throughout the intervention and follow-up time points are completed without any involvement of the researchers. The clinical interview is done by an independent assessor, who is blind to treatment allocation. All personnel involved in the blood and saliva samples are blinded to intervention allocation. Due to the nature of the interventions, participants cannot be completely blinded to allocation.

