## **TRIAL POPULATION AND DESCRIPTIVE ANALYSES**

### **Representativeness of Study Sample and Patient Throughout**

Paramedic students aged 18 and above in the years 1, 2 or 3 of their paramedic training programme are eligible for the study. They are screened for levels of PTSD and MD, and a trained research assistant under supervision of the Principal Investigator will contact participants if they score in the clinical range on measures of PTSD or MD, or report suicidal ideation to evaluate whether they are eligible or need treatment. Participants will be excluded from the study if their symptoms are interfering with their lives and they would like treatment, and the research assistant will then offer information on evidence-based treatment in their local area.

The flow chart of participants through each stage of the trial, including numbers of participants randomly assigned, receiving the intervention, completing the study protocol, and analysed for the primary outcome is provided following current CONSORT guidelines.

Protocol violations or deviations and information relating to the screening data including potential numbers of ineligible patients randomised, together with reasons, are also described.

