## **Analysis Methods**

Analyses of the primary trial objectives:

To analyse any differences between the intervention arms in terms of effectiveness with regards to rates of PTSD and MDD diagnoses (SCID-5) at 1-year follow-up (short-term primary outcome time point) and at 2-years follow-up (long-term primary outcome time point once completed), intervention condition and the interaction between intervention time and

intervention group on rates of PTSD and MDD diagnoses, logistic mixed effects models with PTSD and MDD diagnoses as outcomes (short-term outcome 1-year follow-up data, long-term outcome 2-years follow-up once completed) are specified and analysed.

To analyse any differences between the intervention arms in terms of effectiveness with regards to PTSD symptom severity (PCL-5) or MDD symptom severity (PHQ-9) at 1-year follow-up (short-term primary outcome time point) and at 2-years follow-up (long-term primary outcome time point once completed), intervention condition (categorical; iCT-R versus Mind-Online versus Standard practice; level 2) and the interaction between intervention time (categorical; post-intervention, 6-months follow-up; 1-year-follow-up, 2-year follow-up, once completed; level 1) and intervention group on PTSD or MDD symptom severity, linear mixed effects models with either PTSD or MDD symptom severity as outcomes are specified and analysed.

Both repeated assessments and intervention arm are specified as categorical variables for reasons of flexibility in the modelling approach. Repeated assessments/ time, intervention arm, both their interaction effects, and baseline scores and covariates are estimated as fixed effects and random effects are estimated for time (level 1) nested within the participants (level 2). An unstructured variance-covariance matrix is used to model the error correlation structure within the participants. Estimation method is Maximum Likelihood. Normality of the residuals for the outcomes is confirmed visually.

Randomisation has been done by stratification by site, gender, and baseline PTSD symptom severity and MDD symptom severity. Therefore, baseline PTSD symptom severity and MDD symptom severity and randomisation factors are added as covariates in these models. Site is added as random factor in those models. If non-significant, they will not be carried forward into further analyses.

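### The exploratory early-graduation comparison cannot separate early graduation from stage of training, because its reference group is every non-endorser in a trial that enrolled years 1 to 3

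*Combined protocol and SAP*

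**What the plan says.** The comparison is in the SAP under Supplementary/ Additional Analyses and Outcomes, in the part on the main trial analyses and Covid. The index group is defined by "We will compare rates of PTSD and MDD for the sample who score positive on the item" about graduating "early as a result to support the NHS workforce". Its rates are "compared to participants who do not endorse this item". The sentence names no restriction to a year of study, no stratification and no covariate.

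Enrolment spans the whole programme. Protocol 7.1.1 admits students "In years 1, 2 or 3 of student paramedic training", and the SAP section on representativeness repeats this: "Paramedic students aged 18 and above in the years 1, 2 or 3 of their paramedic training". The planned trial period in the Synopsis opens on "16 October 2017". The SAP dates its during-Covid period from 16 March 2020.

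Year of training is not controlled elsewhere. In the SAP, randomisation is "stratified by site, gender and baseline PHQ-9 score" and baseline PCL-5 score; protocol 8.4 does not list year either. For the primary models, SAP Analysis Methods says that "baseline PTSD symptom severity and MDD symptom severity and randomisation factors are added as covariates in these models", with site as a random factor. The Covid section does not mention year.

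**The concern.** A student has to be near the end of the programme to graduate early, so endorsing the item is tied to stage of training. Stage plausibly brings differences in age, clinical exposure and time in the job. The documents themselves treat such factors as relevant. The protocol lists age and trauma exposure among the baseline factors that may influence symptoms (tertiary objective 1), and the SAP background attributes the risk of PTSD and depression to the nature of emergency work.

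The non-endorsers are likely to be a mixture:

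- final-year students who did not graduate early;
- students too early in training for the item to apply;
- possibly people who had already qualified. On a normal timetable, a year 3 student who entered in the first months of the trial would have finished before March 2020. Such a person may already be in paramedic work, yet would count as not exposed to it.

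What is at stake is the interpretation of one exploratory result. A difference could come from stage alone, and a real association could be hidden if late-stage students have lower rates for other reasons. The randomised comparisons of iCT-R, Mind-Online and Standard Practice do not depend on this analysis.

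**Working it through.** The documents state no rate, sample size or effect for this comparison, so there is no figure to reproduce. The check has two parts.

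**Is stage handled anywhere?** The places where it could be handled are the item comparison itself, the stratification factors, the primary-model covariates and the rest of the Covid section. Year of training appears in none of them.

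**How much of a stage difference would pass into the comparison?** Suppose that early graduation has no effect and that only final-year students can endorse. Let s be the share of participants in final year, e the share of those who endorse, rF the rate in final-year participants and rO the rate in all others. Then:

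- rate in endorsers = rF
- rate in non-endorsers = [s(1 − e)·rF + (1 − s)·rO] / [s(1 − e) + (1 − s)]
- share of non-endorsers not in final year = (1 − s) / (1 − s·e)
- spurious difference = (rF − rO) × (1 − s) / (1 − s·e)

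The documents give none of s, e, rF or rO, so all four are assumed: s from 20% to 50%, e from 30% to 90%, rF = 15.8% and rO = 10.6%. The two rates are borrowed only for scale from the SAP section on timing of the final analysis. There they are the 1-year depression rates in the total sample and in earlier non-intervention studies, not rates by year of training.

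Worked example with s = 1/3 and e = 60%: the non-endorser rate is (0.1333 × 0.158 + 0.6667 × 0.106) / 0.80 = 0.0917 / 0.80 = 11.5%. The difference is 15.8 − 11.5 = 4.3 points, with an odds ratio of 1.45.

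| s | e | Non-endorsers not in final year | Spurious difference | Odds ratio |
|---|---|---|---|---|
| 20% | 30% | 85% | 4.4 points | 1.46 |
| 20% | 90% | 98% | 5.1 points | 1.56 |
| 1/3 | 30% | 74% | 3.9 points | 1.38 |
| 1/3 | 60% | 83% | 4.3 points | 1.45 |
| 1/3 | 90% | 95% | 5.0 points | 1.54 |
| 50% | 30% | 59% | 3.1 points | 1.29 |
| 50% | 90% | 91% | 4.7 points | 1.51 |

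With the two rates exchanged, the difference runs from −3.1 to −5.1 points (odds ratio 0.75 to 0.64). With equal rates it is zero. Within final-year participants it is zero throughout, because in this illustration stage is the only way in which the groups differ.

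The part that does not depend on the borrowed rates is the multiplier (1 − s) / (1 − s·e). Over the assumed shares, 59% to 98% of any stage difference, whatever its size or sign, passes into the comparison.

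**The case against.** The strongest reply is that the SAP makes no claim that needs defending. It promises a comparison of rates, under a heading that already calls these analyses exploratory, and attaches no causal estimand, test or decision to it. A reader might infer that the plan mistakes stage of training for an effect of entering work early. The documents do not support that reading. The nearest causal wording is in the preceding sentence, which concerns the questionnaire scored as a continuous variable and used as a covariate. What stands is narrower: the contrast as specified cannot tell the two apart.

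The premise also rests partly on a form that is not shown. The COVID questionnaire is not reproduced and is not in the protocol's schedule of procedures (Appendix B). Who received it, when, and whether it had a not-applicable response are unknown. That only students near graduation could endorse the item is a reasonable inference from its wording, not a documented fact. If the questionnaire went only to final-year students, or if non-applicable answers were set aside, the problem would shrink or vanish. The SAP says neither.

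The illustration can also be challenged, since every input is assumed. That is correct. It shows how a stage difference would pass through, not that one exists.

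None of this removes the point. An exploratory comparison still needs a reference group that can be interpreted, and as written the result could not show which of these situations applies.

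**Conclusion.** The point holds as a limit on interpretation. Any difference in PTSD or MDD rates between endorsers and all non-endorsers cannot be separated from stage of training. This rests on the stated comparator, on enrolment from all three years, on the absence of year from the design and models, and on the inference that the item applies only near graduation.

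The size and direction of any bias are unknown. The 3.1 to 5.1 points are hypothetical; the sign reverses if late-stage students have the lower rates, and the bias disappears if rates do not vary by stage.

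A reader might also infer that restricting to final-year students would isolate the effect of early entry to work. It would not. Restriction deals with stage, but final-year students who left early may still differ from those who stayed through self-selection, site or programme arrangements.

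The primary and secondary randomised analyses are untouched. This is a cheap improvement to one exploratory analysis.

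**What to change.** Amend the sentence in the SAP so that the main version of this contrast compares endorsers with non-endorsers among participants who were in their final year when they completed the COVID questionnaire, with baseline PCL-5 and PHQ-9 as covariates. Year at that date can be derived from year and date of entry, since year is part of the eligibility criteria. This assumes uninterrupted progression, so known interruptions should be checked.

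If final-year numbers are small, stratify by year of training instead. A year with no endorsers adds nothing directly to a stratified contrast, so this may recover little.

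The section is already labelled exploratory, so no new label is needed for that. The addition needed is to describe the result as a non-randomised association that may still reflect self-selection or site.

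The cost is a sentence or two of text, a smaller comparison group and a wider interval. The loss of precision cannot be sized from the documents because they give no numbers by year.
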